### 11.2.3 Cohort Study

Participants registering for HIV care aged 6-15 years will be consecutively enrolled. We anticipate recruiting a minimum of 300 participants (out of the 350 participants who test HIV positive assuming up to 15% will be lost to follow-up). There would be 210 children on ART if 70% meet eligibility criteria to start ART.  The study will have about 80% power to detect a risk ratio of 1.4-2.2 if the proportion of ART-naïve children with the outcome of interest is at least 20% and 60-80% of the cohort takes ART (Table 11.1).

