## 1.3 Methodology

All children aged 6-15 years attending for acute care at primary health care clinics (PHC) in seven high-density suburbs of southwest Harare will be offered routine HIV counselling and testing during a two year period. The effectiveness of PHC-based routine PITC in providing high coverage of HIV diagnosis will be assessed through a prevalence survey for undiagnosed HIV infection in the 8-17 year age-group in the suburbs served by the PHCs. The seven PHCs will also provide decentralised HIV care, including antiretroviral therapy (ART) initiation.

Children who test HIV-positive through PITC at the PHCs will be recruited into an individual randomised trial of a voluntary lay worker (VLW)-delivered intervention to support households of HIV-infected children aged 6-15 years. Participants will be randomly allocated to either a) primary care based HIV care or b) primary care-based HIV care plus treatment support provided by VLWs, aim, aiming for equal number of control and intervention participants in each clinic. The intervention will be delivered over a eighteen month year period, the main outcomes being adherence to ART, and retention in care.

Children receiving HIV care at the PHCs including those recruited into the trial will be recruited into a clinical cohort study. Data from routine clinic visit (including height, weight, clinical symptoms, incident clinical events and adherence) will be collected. In addition, detailed growth monitoring, lung function testing and a psychosocial assessment (i.e. schooling, guardianship, and disclosure) will be carried out at pre-defined intervals. The rate of lung function decline and rates of pubertal development and growth will be compared by ART status, to investigate whether current ART initiation guidelines can prevent or delay progression of chronic lung disease and/or growth failure.

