**Table 11.1: Power to detect risk ratio (RR) for outcomes in ART-naïve compared to**

**ART-exposed children for a given proportion of cohort on ART (total sample=300)**

| **Proportion on ART** | **No. on ART** | **Proportion with outcome in ART Naive** | **Proportion with outcome in ART exposed** | **RR** | **Power** |
| --- | --- | --- | --- | --- | --- |
| 60% | 180 | 50% | 35% | 1.4 | 80% |
| 60% | 180 | 20% | 9% | 2.2 | 82% |
| 70% | 210 | 50% | 35% | 1.4 | 80% |
| 70% | 210 | 30% | 16% | 1.8 | 86% |
| 70% | 210 | 20% | 9% | 2.2 | 86% |
| 80% | 240 | 50% | 36% | 1.4 | 86% |
| 80% | 240 | 20% | 9% | 2.2 | 90% |

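### Table 11.1 overstates the cohort's power: at the stated total of 300 it is about 51-77% (two-sided 5% assumed), not 80-90%, and it must fall, not rise, as the ART-naive group shrinks

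*Protocol*

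**What the plan says.** Section 11.2.3 of the Protocol sizes the clinical cohort. It states: "We anticipate recruiting a minimum of 300 participants (out of the 350 participants who test HIV positive assuming up to 15% will be lost to" [...], the bracket being an allowance for children lost during the study. The figure of 300 is thus already net of loss. It continues: "There would be 210 children on ART if 70% meet eligibility criteria to start ART", which leaves 90 ART-naive. It then claims: "The study will have about 80% power to detect a risk ratio of 1.4-2.2", provided that at least 20% of ART-naive children have the outcome and "60-80% of the cohort takes ART (Table 11.1").

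The title of Table 11.1 sets the comparison as ART-naive against "ART-exposed children for a given proportion of cohort on ART (total sample=300"). The table has seven rows. The first reads "60% | 180 | 50% | 35% | 1.4 | 80"% and the sixth "80% | 240 | 50% | 36% | 1.4 | 86"%. The columns are share on ART, number on ART, proportion with the outcome in naive children, proportion in exposed children, risk ratio and power. No alpha, sidedness or test is given for the cohort.

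Section 1.3 describes the comparison that the cohort is meant to support: "The rate of lung function decline and rates of pubertal development and growth will be compared by ART status".

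**The concern.** With the total fixed at 300, every increase in the number on ART is taken from the naive group. The naive group is the smaller one in every row, so moving from 60% to 80% on ART makes the split more unequal and must cost power. The table shows the reverse.

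The cohort is one of the study's three components, and section 1.6 says the results will inform whether guidelines on starting ART need revision. If the stated power is too high, the risk ratios of 1.4 and 2.2 are presented as detectable when the cohort has a materially lower chance of detecting them. The overstatement is greatest where most children are on ART.

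**Working it through.** **Inputs.** From Table 11.1: total 300; number on ART n2 = 180, 210 or 240; naive proportion p1; exposed proportion p2. Hence naive n1 = 300 - n2 = 120, 90 or 60. Assumed, because the protocol does not say: alpha 5% two-sided, pooled variance under the null, no continuity correction.

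**Formula.** With pbar = (n1·p1 + n2·p2)/300,

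- SE0 = sqrt[pbar(1 - pbar)(1/n1 + 1/n2)]
- SE1 = sqrt[p1(1 - p1)/n1 + p2(1 - p2)/n2]
- power = Phi[(p1 - p2 - 1.96·SE0)/SE1]

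**Worked example, row 6** (60 v 240, 50% v 36%, stated 86%): pbar = 0.388, SE0 = 0.0703, SE1 = 0.0716. Then (0.14 - 1.96 × 0.0703)/0.0716 = 0.03, so power = 51%.

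**All rows.**

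| Naive v on ART | Proportions | Stated | Two-sided 5% | Exact power of the chi-square test | One-sided 5% |
|---|---|---|---|---|---|
| 120 v 180 | 50% v 35% | 80% | 73.5% | 73.6% | 82.8% |
| 120 v 180 | 20% v 9% | 82% | 77.1% | 78.0% | 85.1% |
| 90 v 210 | 50% v 35% | 80% | 68.1% | 68.4% | 78.3% |
| 90 v 210 | 30% v 16% | 86% | 77.3% | 78.0% | 85.1% |
| 90 v 210 | 20% v 9% | 86% | 73.3% | 74.0% | 81.6% |
| 60 v 240 | 50% v 36% | 86% | 51.2% | 51.3% | 63.3% |
| 60 v 240 | 20% v 9% | 90% | 64.8% | 64.2% | 73.9% |

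**Trend.** For 20% v 9% the recalculated power goes 77.1, 73.3, 64.8%; the table has 82, 86, 90%. One-sided, it still falls: 85.1, 81.6, 73.9%. For the 50% rows the table goes 80, 80, 86%, although the last of these also has a slightly smaller difference (50% v 36%), which should lower power further.

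**Attempts to reproduce the stated column at a total of 300.** With a two-sided 5% test, none of the pooled, unpooled, continuity-corrected, log risk ratio, arcsine, exact chi-square or Fisher calculations brings any row within 2 points. Lowering p2 by 0.005 to allow for rounding brings in row 2 only (81.1%). Using 350 instead of 300 brings in rows 1 and 2 only (79.9% and 82.9%).

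**A possible cause.** Putting the on-ART number in both groups, with a continuity correction, gives 79.4, 80.6, 85.6, 91.2, 86.8, 85.5 and 91.1%. Five of these (rows 1, 2, 5, 6 and 7) lie within 2 points of the stated values. Such groups would total 360, 420 and 480.

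**Risk ratio detectable with 80% power at a total of 300** (same formula, solved for p2):

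| On ART | Naive 50% | Naive 30% | Naive 20% |
|---|---|---|---|
| 60% | 1.48 | - | 2.31 |
| 70% | 1.52 | 1.93 | 2.45 |
| 80% | 1.64 | - | 2.83 |

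**The case against.** Several points on the other side stand.

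- The protocol gives no alpha or test for the cohort, so the replacement figures are conditional. With a one-sided 5% test, rows 3 and 4 come within 2 points of the stated values. That test still misses row 5 by about 4 points and the two rows at 80% on ART by 23 and 16 points (86 - 63.3 and 90 - 73.9), and its trend still falls. Unpooled variance lowers the two-sided range to about 50-74%.
- The equal-groups explanation is an inference. It needs a continuity correction: without one, equal groups give 82.4, 84.5, 87.8, 92.9, 89.6, 87.5 and 93.1%, and only row 6 is within 2 points. The finding does not depend on it.
- The worst row should not stand for the table. Near-even odds of missing the effect apply to one row of seven. In the protocol's own working case of 70% on ART, power is 68-77% against a stated 80-86%; at 60% on ART the gap is about 5-7 points.
- This is the observational cohort. The randomised trial's power is stated separately in section 11.2.1 and is untouched. The table treats a generic binary outcome, so it does not give the power of longitudinal comparisons of lung function or growth, and a reader should not infer that the whole third aim stands or falls with it.

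A reader might also infer that the protocol plans a crude comparison confounded by the reasons for starting ART. The document does not support that. It says only that outcomes are compared by ART status, fixes no unadjusted analysis, and may leave adjustment and changing ART status to a statistical analysis plan that is not shown.

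**Conclusion.** The power column of Table 11.1, and the sentence in section 11.2.3 that claims about 80% power, do not follow from the stated total of 300. The upward trend for 20% v 9% is wrong whatever alpha or test is chosen. The size of the error depends on assumptions that the protocol leaves open: with a two-sided 5% test and no continuity correction, power is about 51-77% (51-78% by exact calculation) against a stated 80-90%; with a one-sided 5% test it is 63-85%. The shortfall is small at 60% on ART and large at 80% on ART (51% against 86%, and 65% against 90%). The conclusion is confined to the cohort's stated precision for a binary outcome.

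**What to change.** In section 11.2.3, state the alpha, sidedness and test for the cohort comparison. Recalculate the power column of Table 11.1 with the actual groups (120 v 180, 90 v 210, 60 v 240), and add a column with the number of ART-naive children so that the split is visible. Under two-sided 5% without continuity correction the column would read about 74, 77, 68, 77, 73, 51 and 65%.

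Replace the sentence claiming about 80% power for risk ratios of 1.4-2.2 with the ratios detectable at 80% power: about 1.5-1.6 when 50% of naive children have the outcome, 1.9 when 30% do (70% on ART), and 2.3-2.8 when 20% do, each over the stated range of ART uptake. If the authors choose another alpha or test, these figures change and should be recomputed to match.

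The cost is a corrected table and less favourable stated precision. Enrolment, follow-up and the randomised trial do not change.

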**Table 11.1: Power to detect risk ratio (RR) for outcomes in ART-naïve compared to**

**ART-exposed children for a given proportion of cohort on ART (total sample=300)**

| **Proportion on ART** | **No. on ART** | **Proportion with outcome in ART Naive** | **Proportion with outcome in ART exposed** | **RR** | **Power** |
| --- | --- | --- | --- | --- | --- |
| 60% | 180 | 50% | 35% | 1.4 | 80% |
| 60% | 180 | 20% | 9% | 2.2 | 82% |
| 70% | 210 | 50% | 35% | 1.4 | 80% |
| 70% | 210 | 30% | 16% | 1.8 | 86% |
| 70% | 210 | 20% | 9% | 2.2 | 86% |
| 80% | 240 | 50% | 36% | 1.4 | 86% |
| 80% | 240 | 20% | 9% | 2.2 | 90% |

# LABORATORY METHODS

## 12.1 Standard Operating Procedures

The Standard Operating Procedures used in the laboratory are shown in Appendix 18.7.

## 12.2 Diagnostic and anonymised HIV testing

For the HIV prevalence survey, participants will be asked to provide an oral mucosal test (OMT) sample for anonymised testing. The samples will be read on the same day. Each of the specimen containers will only bear the study ID of the participants. Diagnostic HIV testing in PHCs will be carried out according to National guidelines. Two rapid tests (Abbott Determine™ and SD Bioline™) will be run in parallel with a 3rd rapid test (INSTI™) with used as a tiebreaker in case of discordant results between the first two tests.

Urine or DBS samples will be collected from participants to check for presence of ART. Urine samples of participants with HIV-positive OMT results will be individually tested for presence of ART. Urine samples of participants with HIV-negative result will be pooled (20 samples pooled) with individual testing of each sample should one pooled batch test ART-positive. DBS samples will be tested individually for ART.

## 12.3 CD4 count and viral load testing

CD4 count testing will be performed at the Beatrice Road Infectious Disease Hospital (BRIDH) laboratories using flow cytometry (PARTEC™). The BRIDH processes CD4 counts for all HIV-infected patients accessing care in City Health Services. Samples for Viral loads will be collected as DBS and outsourced for testing to the National Institute of Health Research (NIHR), Harare.

## 12.4 Processing and storage of blood specimens

Heparinised blood (10ml) will be collected at specified intervals during the study. Plasma, PBMC and DNA will be extracted and stored for use in immuno-genetic studies.

## 12.5 Safety issues

Staff training will be given to all employees given regarding universal precautions and avoidance of needle-stick injuries. A policy for needle-stick injuries is in place (Appendix 18.12). Residual specimens, used specimen containers and laboratory waste will be placed in sealed autoclaved bags, autoclaved, and incinerated at the end of each working day.

A quality management system is in place, with regular external audit of laboratory procedures.

# ADMINISTRATION AND MONITORING

## 13.1 Community Advisory Group

A Community Advisory Group (CAG) will be established in each study suburb to provide early feedback on any problems or community concerns, and enable rapid identification and rectification of any areas of concern. The Community Advisory Group will include members from the community and will meet initially as often as members feel appropriate, and then 6 monthly. Preliminary meetings with the CAGs will be conducted to introduce the study, and representatives of the CAGs will subsequently meet with the ZENITH Field Manager every three months.

## 13.2 Trial Steering Committee

A Trial Steering Committee (TSC) will be established and will advise on the conduct of the study and on logistical issues that arise during the project. The TSC will meet within three months of the start of recruitment and annually thereafter.

## 13.3 Good Clinical Practice

The principles of GCP will be adhered to, and the study team will have in-house GCP training. Modified GCP guidelines suitable for community-randomised public health interventions in resource poor settings will be developed for in-house training purposes.

## 13.4 Monitoring and audit

Project managers and supervisors will be responsible for day-to-day monitoring. Project meetings attended by all field staff will be held each fortnight, during which any problems encountered problems will be discussed and refresher training will be provided.

Internal audits will be conducted within three months of starting the intervention, and not less than annually during the intervention stage. These will include audit of study documentation, data storage, protocol adherence and SAE and incident reporting. A report will be circulated among the project team. [name] will responsible for ensuring that problem areas identified during the audits are rectified, and for circulating details of actions to be taken by the study team.

The MRCZ carry out external audit of all research projects in Zimbabwe, and will conduct one or more audits of ZENITH during the tenure of the project. Otherwise, no external audit will be carried out. An external audit of BRTI finances is conducted annually and the ZENITH project will participate in this audit. In the context of the current trial, safety concerns are minimal; hence a Data Safety Monitoring Board (DSMB) has not been established and no interim analysis is planned.

# ETHICAL CONSIDERATIONS

## 14.1 Participant information leaflets

Leaflets will be produced at a level understandable by children and guardians. These will explain the nature of the trial, making it clear that the intervention is a research study. Separate leaflets will be produced for the anonymised HIV prevalence survey, providing information on where to access HIV testing, including names of health facilities and contact numbers of senior study personnel.

## 14.2 Consent

Written (or witnessed in the case of illiterate participants) informed consent /assent will be taken for: -

- Participation in formative research that will inform the design of the household support intervention (CBO, caregiver and HCW consent)
- Participation in the household support trial (child assent and guardian consent)
- Additional clinical assessment carried out as part of the clinical cohort study or assent (CBO, caregiver and HCW consent)
- The post-PITC HIV prevalence survey (CBO, caregiver and HCW consent)
- Monitoring and evaluation of the intervention through interview of VLWs (VLW consent)
- Storage of blood samples, including DNA (CBO, caregiver and HCW consent)

A guardian will be defined as someone who is over the age of 18 years who is responsible for the daily care, welfare and management of the rights of a minor (someone aged <16 years). The guardian does not necessarily have to be related to the child. If the biological parent is alive but absent (not providing daily care for the child), the individual responsible for the daily welfare of the child will be eligible to give consent. However, the guardian will be encouraged to contact the biological parent (if possible) for consent. If there is disagreement between the guardian and the child about participating in the study or undergoing HIV testing, both will be counselled until consensus is reached.

Children will require the consent of a guardian to undergo HIV testing. We request a waiver for written consent for provider-initiated HIV testing, as this is the recommended “standard of care” in Zimbabwe. An eligible child attending for primary care without a guardian will be given a flyer containing information about HIV testing services available at the clinic and encouraged to return for testing with their guardian. However, if the child has symptoms consistent with immunosuppression, they may be tested as part of clinical management with consent provided by a physician. Additionally, consent for testing could be applied for from social care services if it is in the child’s best interest to test and the child has no named guardian.

Emancipated minors i.e. participants who are married, have children or are the main care-givers for their younger siblings will be able to give consent independently for HIV testing and for participation in the study.

Those who test HIV-positive will be eligible for ongoing HIV care at the facility regardless of whether they consent to participate in the trial or in the cohort study.

## 14.3 Disclosure of HIV status

Post-test HIV counselling will be provided jointly to the guardian and to the participant. Children will be told their HIV status according to their level of understanding and maturity. The child’s HIV status will not disclosed to any health care worker without the consent of the guardian and child. A guardian attending with a child who has previously been tested but is unaware of his/her HIV status will be offered counselling and support to facilitate disclosure.

## 14.4 Ethics Committees providing review and approval

Application has been made to the ethics Committee of the London School of Hygiene And Tropical Medicine. Ethical approval has already been granted by the Institutional Review Board of the Biomedical Research and Training Institute and by the Medical Research Council of Zimbabwe (MRCZ).

## 14.5 Confidentiality

Participants’ identification data will be required for the registration process. Original databases will be stored with a field key file and a soft copy of the coded questionnaires. Alongside original data, anonymised databases will be created for use at the analysis stage.

## 14.6 Indemnity

The London School of Hygiene & Tropical Medicine holds Public Liability ("negligent harm") and Clinical Trial ("non-negligent harm") insurance policies which apply to this trial.

## 14.7 Trial registration

The trial has been registered with the Pan African Clinical Trials Registry (<http://www.pactr.org/>): Trial number-PACTR201212000442288

# STUDY TIME LINE

| **Activity (quarterly)** | **2012** | | | | **2013** | | | | | **2014** | | | | | **2015** | | | | | **2016** | | |
| --- | --- | --- | --- | --- | --- | --- | --- | --- | --- | --- | --- | --- | --- | --- | --- | --- | --- | --- | --- | --- | --- | --- |
| 2 | 3 | 4 | 1 | | 2 | 3 | 4 | 1 | | 2 | 3 | 4 | 1 | | 2 | 3 | 4 | 1 | | 2 | 3 |
| ***Miscellaneous*** |  |  |  |  | |  |  |  |  | |  |  |  |  | |  |  |  |  | |  |  |
| Equipment purchase and shipping |  |  |  |  | |  |  |  |  | |  |  |  |  | |  |  |  |  | |  |  |
| Regulatory approvals |  |  |  |  | |  |  |  |  | |  |  |  |  | |  |  |  |  | |  |  |
| Staff recruitment and GCP training |  |  |  |  | |  |  |  |  | |  |  |  |  | |  |  |  |  | |  |  |
| Training in HIV management & Lung function |  |  |  |  | |  |  |  |  | |  |  |  |  | |  |  |  |  | |  |  |
| ***PITC and VLW Trial*** |  |  |  |  | |  |  |  |  | |  |  |  |  | |  |  |  |  | |  |  |
| Develop data collection tools |  |  |  |  | |  |  |  |  | |  |  |  |  | |  |  |  |  | |  |  |
| Lead in period & attendance data from PHCs |  |  |  |  | |  |  |  |  | |  |  |  |  | |  |  |  |  | |  |  |
| Pilot PITC in PHC |  |  |  |  | |  |  |  |  | |  |  |  |  | |  |  |  |  | |  |  |
| PITC intervention |  |  |  |  | |  |  |  |  | |  |  |  |  | |  |  |  |  | |  |  |
| Cross-sectional HIV survey |  |  |  |  | |  |  |  |  | |  |  |  |  | |  |  |  |  | |  |  |
| Development of tools for formative research |  |  |  |  | |  |  |  |  | |  |  |  |  | |  |  |  |  | |  |  |
| Fieldwork to inform VLW intervention |  |  |  |  | |  |  |  |  | |  |  |  |  | |  |  |  |  | |  |  |
| Development of intervention |  |  |  |  | |  |  |  |  | |  |  |  |  | |  |  |  |  | |  |  |
| Recruitment & training of VLW |  |  |  |  | |  |  |  |  | |  |  |  |  | |  |  |  |  | |  |  |
| Enrolment into trial |  |  |  |  | |  |  |  |  | |  |  |  |  | |  |  |  |  | |  |  |
| VLW-household intervention |  |  |  |  | |  |  |  |  | |  |  |  |  | |  |  |  |  | |  |  |
| Process evaluation of intervention |  |  |  |  | |  |  |  |  | |  |  |  |  | |  |  |  |  | |  |  |
| Health economics |  |  |  |  | |  |  |  |  | |  |  |  |  | |  |  |  |  | |  |  |
| Data analysis |  |  |  |  | |  |  |  |  | |  |  |  |  | |  |  |  |  | |  |  |
| Manuscript preparation & submission |  |  |  |  | |  |  |  |  | |  |  |  |  | |  |  |  |  | |  |  |
| ***Clinical Cohort Study*** |  |  |  |  | |  |  |  |  | |  |  |  |  | |  |  |  |  | |  |  |
| Cohort recruitment |  |  |  |  | |  |  |  |  | |  |  |  |  | |  |  |  |  | |  |  |
| Cohort follow-up |  |  |  |  | |  |  |  |  | |  |  |  |  | |  |  |  |  | |  |  |
| Data analysis |  |  |  |  | |  |  |  |  | |  |  |  |  | |  |  |  |  | |  |  |
| Manuscript preparation & submission |  |  |  |  | |  |  |  |  | |  |  |  |  | |  |  |  |  | |  |  |

# DISSEMINATION

Results will be shared through six monthly meetings with the Department of City Health and the MOHCW. Results of interim data analysis will be presented at national research meetings, such as the annual research day held by the Institute of Continuing Health Education (ICHE) of the University of Zimbabwe and presented at international research meetings. Results will be prepared for publication in international peer reviewed scientific journals.

